## BACKGROUND INFORMATION AND STUDY RATIONALE

Aneurysmal subarachnoid haemorrhage (aSAH) is associated with high morbidity and mortality with an incidence of 5-9 per 100,000 population. The incidence of aSAH peaks amongst those of 40-60 years[1, 8]; aSAH carries a high overall mortality rate of up to 67% [2, 8] with only around half of the survivors able to live independently. Given the age-related incidence and high morbidity and mortality, SAH has a high burden on society [3].

Conventionally following SAH, treatment is directed to securing the aneurysm to prevent further re-bleed. This however does not improve morbidity and mortality due to the haemorrhage. The only approved effective treatment to reduce morbidity is nimodipine [4]; its effects are small and despite its use, poor outcomes remain a significant problem [5]. Even in survivors conventionally considered to have made a good recovery, neurocognitive deficits are common, leading to extensive problems with social reintegration and functioning [6].

NicaPlant® is a modified release formulation of the calcium channel blocker nicardipine free base, and it is presented in the form of a rod shape implant (2 mm x 10 mm, 4 mg nicardipine load). The excipients used in the formulation for sustained release are a mixture of two completely degradable and fully synthetic (no animal sourced) polymers (Poly(D,L-lactide-co-glycolide), PLGA), with different molecular weights composed of a 50 : 50 ratio of lactate and glycolate.

NicaPlant® will be used to treat patients affected by aSAH at the time of aneurysm closure by surgical clipping.

In these patients, NicaPlant® will be placed in close proximity to the blood vessel walls within the basal cisterns at the time of the microsurgical aneurysm treatment, in order to locally deliver the active pharmaceutical ingredient (API) and prevent cerebral vasospasm (CV), cerebral infarction and delayed ischemic neurological deficit (DIND). CV and DIND are known to be major causes of death following aneurysm treatment and to be responsible for poor long term prognosis and disability in patients surviving aSAH [1, 8].

This procedure has already been successfully performed with a pharmaceutical equivalent known as nicardipine prolonged-release implants (NPRI) in over 250 aSAH patients. Up to 12 implants were used demonstrating excellent safety and tolerability profiles with no complications reported and no signs of neuronal toxicity or chemical meningitis [9, 10, 11, 12, 13]. All these studies demonstrated prevention of CV in vessels adjacent to the site(s) of implantation and decreased cerebral infarction and DIND. However, most of these studies lacked a control group.

NicaPlant® is a pharmaceutical equivalent of the NPRI; it has the same shape and size, same nicardipine free base load, similar excipient composition and comparable *in vitro* release profile.

In a recent phase IIa study the safety and tolerability of increasing doses (3, 6, 10 and 13 implants in 2, 2, 3 and 3 patients, respectively) was tested.

Eight serious adverse events occurred during the study that can be easily explained by the severe status of the patients and the major surgery. Five serious adverse events were classified as possible or probable related to the treatment either because of the lack of other explanations or, even if other explanations were more likely, a connection to the implants was still supposable. The variety of adverse events that can be suspected, already by developing a subarachnoid haemorrhage and the following clip ligation, and especially by reason of the small group a statistical evaluation of adverse reactions is not expedient.

The results of the phase IIa study overall demonstrate that NicaPlant® was safe and well tolerated. No obvious advantage from an exposure perspective could be observed with 13 versus 10 implants. More details of this study are presented in the Investigator's Brochure.

### **Investigational agent**

NicaPlant® is a nicardipine modified release formulation, it is presented in the form of a rod shaped implant (2 mm x 10 mm, 4 mg nicardipine load).

### **Preclinical data**

The prevention of cerebral vasoconstriction in dogs with subarachnoid haemorrhage by nicardipine-releasing implants comparable to NicaPlant® has been demonstrated in different published investigations. In addition, under conditions of global cerebral ischaemia, nicardipine was shown to improve cerebral blood flow and to prevent ischaemic cerebral tissue damage and improve recovery from damage in dogs, rats and gerbils *in vivo*. Furthermore, the pharmacodynamic activity of nicardipine as vasodilating agent has been demonstrated in various animal models as general vasodilatation and as vasodilatation with increase of blood flow in the arterial beds of different organs in rats, dogs and monkeys.

Secondary pharmacodynamic effects of nicardipine were seen as anti-oxidant and anti-neuroinflammatory activities, activities which may contribute to the therapeutic effect.

Published investigations on safety pharmacology demonstrated, in accordance with the investigations on primary pharmacology, a general improvement of blood flow in the major organ systems such as heart, central nervous system, gastrointestinal tract and kidneys. Under conditions of experimental infarction in the heart or central nervous system, nicardipine reduced the infarct size and improved tissue recovery as well as revascularisation. Besides a reduction of renal blood flow in hypertensive rabbits, which was not seen in normotensive rabbits, no adverse effects of nicardipine were seen in safety pharmacology studies.

Most probably based on the improved blood flow in major organs, nicardipine may reduce the toxicity of other drugs.

NicaPlant® brain local tolerance has been assessed in mice using implant slices. No development of local reactions was observed by intravital microscopy and by immunohistochemistry, while occurred the expected vasodilation.

Full details of the preclinical data are described in the Investigator's Brochure.

108 **Risks / benefits**

109 The potential therapeutic benefits of NicaPlant® outweigh any potential risks for patients with  
110 aSAH. NPRI has already demonstrated good safety and tolerability profiles with no drug-  
111 related adverse events; in particular, there have been no observed significant differences in  
112 the incidence of central nervous system infection or hydrocephalus. Furthermore, all previous  
113 NPRI studies demonstrated prevention of CV in vessels adjacent to the site(s) of implantation  
114 and decreased cerebral infarction and DIND.

115 NicaPlant® is a pharmaceutical equivalent of the NPRI. It has the same shape and size,  
116 meaning the implantation procedure remains unchanged in risk profile from previous studies.  
117 The API (nicardipine free base) load is unchanged with a similar excipient composition  
118 leading to a comparable *in vitro* release profile.

119 Overall NicaPlant® was safe and well tolerated in the Phase IIa study. The patient number  
120 per group was too small to perform differential statistics but regarding the current safety data  
121 available, the potential therapeutic benefit still outweighs the potential risks. The implants  
122 have proven to be easy to implant, as stated by investigators, and the DSMB assessed the  
123 benefits and risks at every meeting before allowing the progression to the next dosing level.  
124 In the DSMB's final meeting, after reviewing adverse events and pharmacokinetics, the board  
125 decided that there seems to be no additional benefit after the dose progression from 10 to 13  
126 implants.

127  
128 The proposed clinical study is a randomised, single-blind, parallel-group design comparing  
129 NicaPlant® implants versus standard of care in 40 patients who have had aSAH.

130 The two groups of patients will be subjected to the following treatments:

131 • Standard of care plus NicaPlant®.

132 • Standard of care.

133 Both groups of patients will receive the standard of care according to treatment guidelines [8]  
134 and all further medical care will not be different between the groups. Patients in the  
135 interventional group will only in addition receive NicaPlant® implants.

136 NicaPlant® will be administered by placement during microsurgical clipping of the ruptured  
137 aneurysm in proximity to all of the exposed cerebral blood vessels.

138 Patients will be assessed to determine the efficacy of NicaPlant® application to reduce the  
139 occurrence of cerebral vasospasm and to prevent early morbidity/mortality following aSAH.  
140 Cerebral vasospasm will be assessed by analysis of angiograms to determine narrowing of the  
141 proximal blood vessels. A cerebral vasospasm is defined as lumen reduction  $\geq 33\%$

142 Safety assessments will be made to confirm the safety and tolerability of the selected dose of  
143 NicaPlant® up to patient discharge, or day 21, whichever occurs first.

144 Clinical Outcomes will be recorded at 12 weeks and 1 year (week 52) after the aSAH.

145 A data safety monitoring board (DSMB) will be set-up to monitor safety throughout the trial  
146 period and provide recommendations for any necessary actions. A steering committee will  
147 receive and review the reports from the DSMB and take action as appropriate.

The final analysis will be carried out when the final patient completes the week 12 assessment. Data collected for patients at Week 52 after aSAH will be analysed and included as an addendum to the final report.

Given that NicaPlant® is implanted at the time of aneurysmal clipping, it should be emphasised that the investigational product cannot be withdrawn after implantation.

In summary, published data on the safety and effectiveness of NPRIs supports the premise that NicaPlant® offers significant potential therapeutic benefits, without significant clinical risk.

Furthermore, the results of the phase IIa study involving a total of 10 actively treated patients (with 2 patients each in 3 and 6 Implant groups and 3 patients each in 10 and 13 Implant groups) demonstrate that NicaPlant® was safe and well-tolerated up to 13 implants/ patient.

## **Study Rationale**

This is a Safety, Tolerability, Efficacy and Pharmacokinetic study of NicaPlant® in Subarachnoid Haemorrhage involving two treatments groups, standard of care and those receiving standard of care and the investigational product NicaPlant®. Those randomised to the investigational group will receive NicaPlant® in order to improve and reduce the long-term complications of aSAH such as CV & DIND.

The objective is to assess the efficacy of NicaPlant® in preventing the occurrence of angiographic cerebral vasospasm following aSAH and its complication till patient discharge or day 21, whichever occurs first; clinical outcomes will be assessed by rating scales at 12 and 52 weeks.

## **Trial conduct**

This study will be conducted in compliance with the protocol and according to Good Clinical Practice and applicable regulatory standards. No deviation from the protocol will be implemented without the prior review and approval by the relevant ethics and regulatory authorities, except where it may be necessary to eliminate an immediate hazard to a research subject. In such case, the deviation will be reported to the relevant ethics and regulatory authorities as soon as possible.

## **Population**

The population to be studied are patients with spontaneous aSAH, World Federation of Neurological Surgeons (WFNS) grade III-IV, who present within 48 hours of ictus and that clip ligation of the aneurysm is achievable within 72 hours of aSAH (in the opinion of the Investigator).

Patients with WFNS grade I, II and V are excluded from this study.

This decision is based on the recent publication of results of the NEWTON 2 study, that investigated the activity of EG-1962, microparticle containing nimodipine and delivered via an EVD to aSAH patients, indicated that the compound even if able to significantly reduce occurrence of CV compared to the control group, had no effect in improving the percentage of patient presenting a 90 days good clinical outcome in grade I and II patients (GOSE 6-8; EG-1962: 46%, control: 55% ), therefore posing only potential additional risks for these patients (D Hänggi et al., for the NEWTON 2 Investigators, International Stroke conference, 6-8, Feb, 2019, Honolulu, Hawaii).

## **STUDY OBJECTIVES AND ENDPOINTS**

### **Primary objective**

- To assess the efficacy of local nicardipine application via controlled-release polymers (NicaPlant®) in preventing the occurrence of cerebral vasospasm following aneurysmal Subarachnoid Haemorrhage (aSAH), by evaluating the incidence of moderate to severe cerebral angiographic vasospasm assessed by digital subtraction angiography (DSA).
- To assess the safety and tolerability of the selected dose of NicaPlant® (10 implants).

### **Secondary objectives**

- To assess the efficacy of local nicardipine application via controlled-release polymers (NicaPlant®) on:

227 Incidence of new cerebral infarcts on CT of the brain performed at Day 14  $\pm$  1 post-  
228 aneurysm rupture, or before patient discharge, versus post-intervention (i.e. post clip  
229 ligation and NicaPlant® implantation) CT scan.

230

### 231 **Exploratory objectives**

- 232 • To assess the efficacy of local nicardipine application via controlled-release polymers  
233 (NicaPlant®) on:

234 Incidence of vasospasm-related morbidity/mortality within 21 days post-aneurysm  
235 rupture or before patient discharge, defined by at least one of the following:

- 236 ○ DIND.
- 237 ○ Death caused by vasospasm, delayed ischemic neurological deficit (DIND),  
238 infarcts or complications due to anti-vasospasm therapy.
- 239 ○ The need for anti-vasospasm rescue therapy before patient discharge or within  
240 21 days post-aneurysm rupture.

- 241 • To assess the pharmacokinetic profile of NicaPlant® (local nicardipine application via  
242 polymers) in plasma and its levels in CSF (only in patients provided with an EVD at  
243 time of CSF removal for medical reasons).

- 244 • To assess the effect on clinical outcome and mortality following aSAH at week 12.

- 245 • To assess the effect on clinical outcome and mortality following aSAH at Week 52.

### 246 **Primary Outcome Endpoints**

247 The primary outcome endpoints are:

#### 248 ***Safety:***

#### 249 **Daily assessments:**

- 250 • Adverse events (AEs)
- 251 • Shunt-dependent hydrocephalus (to Day 21 $\pm$ 1 or patient discharge)
- 252 • Bacterial meningitis (to Day 21 $\pm$ 1 or patient discharge)
- 253 • Change in grading of AE severity

254

#### 255 **At the defined visits 1 to 5:**

256

- 257 • Vital Signs: blood pressure, pulse rate, respiratory rate and body temperature

- 258 • Electrocardiogram (ECG)

- 259 • Full blood count, urea and electrolytes, liver function tests, C-reactive protein

260 Safety assessments will be made from baseline until discharge or day 21±1 and at all  
261 subsequent visits. Adverse Events occurring after day 21±1 will be collected but will no  
262 longer be considered treatment emergent.

## 263 *Efficacy:*

### 264 **Primary efficacy endpoint**

- 265 • Incidence of moderate to severe cerebral angiographic vasospasm after aneurysmal  
266 subarachnoid haemorrhage, where angiographic vasospasm is defined as a  $\geq 33\%$   
267 reduction in diameter in at least one vessel segment by comparison to preoperative  
268 angiography.

### 269 270 **Secondary Outcome Endpoints**

271 The secondary outcome endpoints are:

- 272 • Incidence of new cerebral infarcts on CT scan at day  $14 \pm 1$ , or before patient  
273 discharge (compared with postoperative CT scan).

274

### 275 **Exploratory Outcome Endpoints**

276 The exploratory outcome endpoints are:

- 277 • Incidence of vasospasm-related morbidity/mortality within 21 days or before  
278 patient discharge, defined by at least one of the following:
  - 279 a. DIND.
  - 280 b. Death caused by vasospasm, delayed ischemic neurological deficit (DIND),  
281 infarcts or complications due to anti-vasospasm therapy.
  - 282 c. The need for anti-vasospasm rescue therapy.
- 283 • Length of Intensive Care Unit (ICU) stay
- 284 • Length of Hospital Stay
- 285 • Clinical outcome at Week 12 post-aneurysm rupture as measured by:
  - 286 a. Modified Rankin Scale (mRS) – “Good Outcome” defined as mRS of 0 to 2
  - 287 b. Glasgow Outcome Scale (Extended) (GOSE) – “favourable outcome” of 6-8,  
288 “unfavourable outcome” of 0-5
  - 289 c. Montreal Cognitive Assessment tool (MoCA) - score 0-30 higher better
  - 290 d. Health related quality of life assessed using the EQ-5D-5L and SF36.

- Long-term Clinical outcome at Week 52 post-aneurysm rupture as measured by:
  - a. Modified Rankin Scale (mRS) – “Good Outcome” defined as mRS of 0 to 2
  - b. Glasgow Outcome Scale (Extended) (GOSE) – “favourable outcome” of 6-8, “unfavourable outcome” of 0-5
  - c. Montreal Cognitive Assessment tool (MoCA) - score 0-30 higher better
  - d. Health related quality of life assessed using the EQ-5D-5L and SF36.

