### 375 ***Blinding***

376 The study design does not include a placebo implant for ethical reasons; therefore, it is not  
377 possible to blind the neurosurgeons performing the aneurysmal clipping procedure to study  
378 treatment. Accordingly, the standard of care control group will receive no intracranial  
379 treatment (i.e., no placebo implants).

380 Patient selection bias is controlled by randomisation; patients will be blinded to which  
381 treatment they are receiving (implant or standard of care group) throughout the study i.e. the  
382 study is single blinded.

383 Therefore, the treatment groups are as follows:

- 384 • Patients receiving standard of care and NicaPlant® implants.

385 OR

- 386 • Patients in standard of care.

387 Patients will be assigned a corresponding randomisation code at consent; in the operation  
388 room, following aneurysm clip ligation, a member of the unblinded operation room team will  
389 verify the randomisation code using the IWRS system; if the patient is to receive NicaPlant®  
390 implants the implantation procedure goes ahead; if not, no implantation is carried out.

391 In emergency situations, when the identity of the treatment arm must be made known, the  
392 treatment arm of the patient will be available to designated and authorised personnel using  
393 the IWRS system. Access to the IWRS is held by the responsible neurosurgeon and other

designated authorised site personnel, to be agreed prior to study commencement. Full details of the randomisation including user access will be provided in the study IWRS user guide.

Study team staff (including those undertaking Safety Assessments, TCD readings, mGCS assessments and Clinical Outcome assessments) will be blinded to the treatment. An independent specialist, also blinded to the treatment, will undertake the analysis of the angiograms and computed tomography imaging of the brain for the diagnosis of cerebral vasospasm and new cerebral infarcts, respectively, for study endpoint assessment.

Trained personnel collecting data on clinical outcome at week 12 and 52 will also be blinded. In cases of DIND or anti-vasospasm rescue therapy as determined by the sites, all required data (e.g. clinical data, case narratives, angiograms, CTs) will be provided to a board of blinded independent experts to adjudicate on the presence of DIND or anti-vasospasm rescue therapy.

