
5. The ratios are to be used to analyse vessel diameters independently from the original magnification used. Angiographic vasospasm is defined as a  $\geq 33\%$  reduction in diameter in at least one vessel segment.
6. Angiographic vasospasm will be also assessed qualitatively as: none/mild (can be more than two major cerebral arteries [segments] with mild (less than 1/3 arterial narrowing) angiographic vasospasm and/or 1 segment with moderate angiographic vasospasm (1/3 to 2/3 arterial narrowing); moderate (at least 2 segments with moderate angiographic vasospasm and/or 1 or 2 segments with severe angiographic vasospasm [more than 2/3 arterial narrowing]); or severe (at least 3 segments with severe angiographic vasospasm). A segment corresponds to a major cerebral artery.
7. Additionally, a semiquantitative rating of the distal vessel segments according to this scheme will be performed.

[figure not shown]

Nomenclature of the basal cerebral arteries of the circle of Willis. ACA, anterior cerebral artery (segments A1, A2); ACoA, anterior communicating artery; BA, basilar artery; CS, carotid siphon (segments C1-C3); ICA, internal carotid artery; MCA, middle cerebral artery (segments M1, M2); OA, ophthalmic artery; PCA, posterior cerebral artery (segments P1, P2); PCoA, posterior communicating artery; VA, vertebral artery.

All CT examinations will be assessed by a neuroradiologist blinded to the clinical data and treatment assignment. Infarct(s) on the CT brain scan performed  $36 \pm 12$  hours postoperatively will be classified as surgery related and related to the respective vessel territory. New infarcts (compared to such postoperative CT) in the CT scan at visit 4 will be classified as vasospasm related and related to the respective vessel territory or to hemodynamic infarction.

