## 1098 **Populations for analysis**

1099 Three main patient analysis sets will be described. These include the Full Analysis Set (FAS),  
1100 Per protocol (PP) and Safety sets. The FAS set is considered the primary analysis set for all  
1101 primary and secondary efficacy endpoints. The PP set will also be used to analyse the  
1102 primary efficacy endpoint and will consist of those patients in the FAS set without any major  
1103 protocol deviations. These will be defined in the SAP. The Safety set is considered the  
1104 primary set for all safety evaluations.  
1105 For the purpose of evaluating PK and PD endpoints, separate Pharmacokinetic and  
1106 Pharmacodynamic analysis sets will be defined.

1107 All available data of deceased patients will be included in the analysis sets.

1108

1109

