1155 -Incidence of morbidity/mortality (DIND; death due to vasospasm, DIND, infarcts or  
1156 complications due to anti-vasospasm therapy) by patient discharge.

1157 -Need of anti-vasospasm rescue therapy by patient discharge.

1158 -Clinical outcomes at week 12 and week 52, following assessment with modified Rankin  
1159 Scale (mRS) scored 0-6 (with incidence of 'Good' outcome scores 0-2) and Glasgow  
1160 Outcome Scale (extended) (GOSE) scored 0-8 (with incidence of 'Favourable' outcome  
1161 scores 6-8), together with the Montreal Cognitive Assessment Tool (MOCA) (score 0-30  
1162 higher better) and Health related quality of life, assessed using the EQ-5D-5L and SF36. The  
1163 Length of stay in hospital and the ICU will also be assessed as measures of clinical outcome .  
1164

1165 The additional information reported as an addendum to the final report will specifically  
1166 include the final assessment for clinical outcome (mRS and GOSE), assessed at week 52,  
1167 together with any additional adverse events (specifically those that are CNS related), together  
1168 with the MOCA, EQ-5D-5L and SF36.

1169 These data can be considered binary, ordered categorical or interval in nature.

1170 All binary outcomes will be evaluated using the same methods as those for the primary  
1171 endpoint (Fishers exact test).

1172 Ordered categorical data will be analysed using the Cochran-Mantel-Haenzel (CMH) test  
1173 (with modified ridits). Ordinal logistic regression may be supplemented if other covariates of  
1174 interest are identified (e.g. age, gender, WFNS).

1175 Normally distributed Interval data will be analysed using an analysis of variance (ANOVA)  
1176 model including treatment group as fixed effect and (if possible) baseline or other  
1177 explanatory variables as covariates (e.g. age, gender, WFNS). Estimates of treatment effects  
1178 and treatment differences will use LS means and 95% confidence intervals.

1179 Non-parametric alternatives, however, will be substituted if these data are non-normally  
1180 distributed (eg: Length of stay). This may take the form of the Wilcoxon rank sum test or a  
1181 ranked based ANOVA model.

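### Exploratory morbidity/mortality composite: an early death from an unlisted cause counts as no event, and cause of death is outside the blinded board's remit

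*Protocol*

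**What the plan says.** Section 2 of the protocol (Exploratory objectives) sets the endpoint as "Incidence of vasospasm-related morbidity/mortality within 21 days post-aneurysm" rupture, or before discharge. The Exploratory Outcome Endpoints repeat it with the rule "patient discharge, defined by at least one of the following": DIND, a death from a listed cause, or need for anti-vasospasm rescue therapy. The death item begins "Death caused by vasospasm, delayed ischemic neurological deficit (DIND" and ends with "infarcts or complications due to anti-vasospasm therapy". Section 8 (Other exploratory endpoints) and section 11 (Efficacy Endpoints) use the same cause-specific death item.

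Three further provisions bear on how a death is scored:

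- Section 4 (Replacement of Withdrawn Patients) treats a patient who dies as a completer who is not replaced. Section 11 (Populations for analysis) adds: "All available data of deceased patients will be included in the analysis sets".
- Section 11 (Efficacy Endpoints) sends the composite to Fisher's exact test: "All binary outcomes will be evaluated using the same methods as those for the primary" endpoint.
- Section 3 (Blinding) sends cases of DIND or rescue therapy, as identified by the sites, to a board of "blinded independent experts to adjudicate on the presence of DIND or anti-vasospasm rescue" therapy. The table of blinded personnel in section 6 gives the board the same two tasks.

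**The concern.** A yes/no endpoint over a fixed window needs a rule for patients who die before they could show the event. Here the only rule is the list of causes. A death from re-bleeding or infection on day 4, with no DIND or rescue before it, satisfies none of the three items, although death removed any chance of a later event. Scored that way, an arm with more early deaths from other causes shows a lower composite rate.

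The list also depends on a judgement about cause. Two of the three components are adjudicated blind. The third, which needs a causal attribution, is given to nobody, and the protocol states no criteria for it.

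At stake is the reading of the only early endpoint that combines morbidity and mortality, in a trial whose design section names early morbidity/mortality as something the implants should prevent.

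**Working it through.** **The plan's own figure.** The protocol gives no rate or power for the composite. Its only power statement concerns the primary endpoint: 20 per arm, 20% against 70%, two-sided 5%, 84% power. Full enumeration of the two binomial distributions with Fisher's exact test gives 84.6%, so that figure reproduces. Nothing below changes it.

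**Scoring of an early other-cause death.** An event needs at least one of DIND, listed-cause death or rescue. The patient has none, is a completer, and stays in the analysis set. The written definition therefore gives no event. This holds only for deaths with no earlier DIND or rescue therapy.

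**Size.** Let *p* be the composite risk in patients who do not die early of another cause, and *d* the risk of an early other-cause death with no earlier component. Both are assumptions; the protocol gives neither.

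- Rate as written: (1 − *d*) × *p*
- Rate with every death counted: *d* + (1 − *d*) × *p*

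For *p* = 50% in both arms and *d* = 15% (NicaPlant) against 5% (control):

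- As written: 0.85 × 0.50 = 42.5% against 0.95 × 0.50 = 47.5%, a difference of −5 points.
- All deaths: 15% + 42.5% = 57.5% against 5% + 47.5% = 52.5%, a difference of +5 points.

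Other values, NicaPlant against control:

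| *p* (both arms) | *d* | As written | Difference (points) | All deaths counted | Difference (points) |
|---|---|---|---|---|---|
| 50% | 5% vs 5% | 47.5% vs 47.5% | 0 | 52.5% vs 52.5% | 0 |
| 40% | 20% vs 5% | 32.0% vs 38.0% | −6 | 52.0% vs 43.0% | +9 |
| 50% | 20% vs 5% | 40.0% vs 47.5% | −7.5 | 60.0% vs 52.5% | +7.5 |
| 60% | 20% vs 5% | 48.0% vs 57.0% | −9 | 68.0% vs 62.0% | +6 |

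With equal *p*, the difference as written is −(*d*₁ − *d*₀) × *p* and the all-death difference is (*d*₁ − *d*₀) × (1 − *p*). Over *p* = 40–60% and *d*₁ = 10–20% against *d*₀ = 5%, each lies between 2 points (0.05 × 0.40) and 9 points (0.15 × 0.60) in absolute size, with opposite signs. With *d*₁ = *d*₀ both are zero.

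**One attribution.** For a death with no earlier DIND or rescue, the assigned cause moves that arm's rate by 1/20 = 5 points.

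**The word infarcts.** Section 8 says that infarcts on the CT at 36 ± 12 "hours postoperatively will be classified as surgery related and related to the respective vessel territory", and its Radiology part defines new infarction so as to exclude the clipping procedure. The death item says only infarcts and points to neither rule.

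**The versions side by side.** The window is 21 days in section 2, 14 days in section 8 (Other exploratory endpoints), and runs to discharge in section 11. Rescue therapy is inside the composite in sections 2 and 8 but listed separately in section 11. Under the section 11 form, a patient who had rescue therapy but no DIND and then died of another cause would also be a non-event.

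**The case against.** The endpoint is exploratory and is named vasospasm-related, so a cause-specific death item is a deliberate and legitimate choice. That stands, and it is why the present version should be kept. The protocol nowhere states the scoring of an early death outright. It follows from the definition and the completer rule, and the SAP that section 11 announces, which is not among the documents, could add a rule. The attribution also matters less than it seems: a death from DIND already counts through DIND, and one from complications of rescue therapy normally counts through rescue.

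Three stronger readings are tempting, and the documents do not support them.

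- *A reader might infer that excess early deaths would go unseen.* They would not. The mRS at Visit 5 has a category for death, mGCS is recorded daily, death is a serious adverse event that enters the safety summaries, and the DSMB reviews unblinded safety data. The mRS and GOSE at weeks 12 and 52 count all deaths. Nor is the composite the only early clinical measure.
- *A reader might infer that unblinded staff decide the cause of death.* The protocol does not say who decides. Only the operating-room team is listed as unblinded; the ICU team and those making safety assessments are listed as blinded.
- *A reader might infer that deaths from surgical infarcts are meant to count.* The endpoint's name points the other way. This is loose wording rather than a stated rule.

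The assumed death rates have no source in the protocol. The exclusion of WFNS grade V and of major complications during repair should make some early deaths rarer. What remains is the scoring gap and the gap in the board's remit.

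**Conclusion.** The point holds in a limited form. As defined, an early death from an unlisted cause with no earlier DIND or rescue therapy is a non-event, and the composite is biased towards the arm with more such deaths. The direction follows from the definition. The size, 2 to 9 points over the ranges above with a reversal of sign once all deaths count, rests wholly on assumed rates and on other-cause deaths differing between arms. Cause of death is the only component without blinded adjudication. The primary and secondary endpoints and the sample size are untouched. This is a cheap improvement to an exploratory endpoint. It is not a reason to replace that endpoint.

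**What to change.** 1. Report the composite with death from any cause beside the cause-specific version, and show each component and the other-cause deaths by arm.
2. In section 3 (Blinding) and the section 6 table, add cause of death to the existing board's remit for every death within the composite's window, with written criteria.
3. State that infarcts in the death item means new infarcts as defined under Radiology in section 8.
4. In the same amendment, reconcile the window across sections 2, 8 and 11, and settle whether rescue therapy belongs inside the composite.

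The cost is protocol wording and a few extra narratives for a board that already exists. The all-cause version carries some noise from deaths unrelated to vasospasm, which is why the cause-specific version stays alongside it.
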